### Rationale for the Study’s Design

As a substitute for being a randomized controlled trial (RCT), this trial is intended to be a single-arm clinical research. This decision was made for two reasons:

Phase of exploration and proof-concept: Assessing the viability and efficacy of osseodensification in enhancing bone density and implant stability in delayed implant placement, especially in locations with D2 and D3 bone quality, is the main goal of this protocol. Before evaluating more extensive comparison studies, a single-arm design enables targeted evaluation of changes over time within the same group of patients, given the paucity of prospective clinical evidence in this field.Ethical and practical considerations: Osseodensification is anticipated to be advantageous for all patients who are enrolled in this trial because they all have poor bone conditions. Participants in a control group undergoing traditional osteotomy may be at increased risk of experiencing inadequate implant stability or failure if this procedure is not used. Consequently, a within-subject repeated measures design was judged to be both ethically and therapeutically appropriate for this exploratory study.

### Primary and Secondary Outcome Variables

This study’s primary outcome variables will involve evaluating bone density and volume changes in delayed implant placement locations using radiographic techniques including CBCT to ascertain how the osseodensification system affects compaction and bone preservation. RFA will be used to determine the ISQ, which is another important component. Additionally, the study will use radiographic techniques to analyze BIC over time in order to evaluate osseointegration success.

The clinical and radiographic evaluation of bone healing, as determined by peri-implant bone level changes using CBCT, will be the main emphasis of the secondary outcome variables. Functional loading results, the absence of implant mobility, and the absence of peri-implant radiolucency will also be used to assess the implant success rate. In order to examine the long-term efficacy and safety of implants placed using the osseodensification system, the study will also monitor complication rates, such as early or late implant failure, marginal bone loss, and the incidence of peri-implantitis.

## Results

### Overview

Since this is a study protocol, no analyzed data are currently available. Recruitment for this pilot single-arm study began in July 2025, following institutional ethics approval and trial registration (CTRI/2025/03/082513). As of October 2025, participant screening and baseline assessments were ongoing. The target sample (N=22) is expected to be fully enrolled by January 2026.

The surgical phase, involving delayed implant placement using the osseodensification technique, is scheduled for completion by month 6 (April 2026). Clinical and radiographic follow-up evaluations, including CBCT-based bone density and implant stability (ISQ) measurements, will be conducted at baseline, 3 months, and 9 months post surgery.

Final data collection and statistical analysis are anticipated by month 12 (July 2026). The study is ongoing, and no outcome data are yet available (Table 2).

**Table 2 table2:** Study timeline outlining recruitment, surgical phase, and follow-up assessments.

Study activity or phase	Timeline	Details
Recruitment start	July 2025	Recruitment initiated; screening and enrollment of eligible participants began
Current status	October 2025	Recruitment and baseline assessments are underway
Expected completion of enrolment	January 2026	Target sample size (N=22) expected to be fully recruited
Surgical phase	April 2026 (month 6)	Completion of delayed implant placement using the OD^a^ technique
Follow-up evaluations	Baseline, 3 months, and 9 months post surgery	Clinical and radiographic assessments for bone density and implant stability (ISQ^b^ and CBCT^c^)
Final data collection and analysis	July 2026 (month 12)	Completion of all follow-ups and commencement of statistical analysis

^a^OD: osseodensification.

^b^ISQ: Implant Stability Quotient.

^c^CBCT: cone beam computed tomography.

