**Results:**

Recruitment began in July 2025, and as of October 2025, screening and baseline assessments are ongoing. Enrolment of 22 participants was expected by January 2026, with the surgical phase expected to be completed by April 2026. Follow-up evaluations will be performed at baseline, 3 months, and 9 months post surgery. Final data collection and statistical analysis are anticipated by July 2026. No outcome data are yet available because the study is ongoing.

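### The timeline closes all follow-up in July 2026, only 3 months after the last planned surgery, although the last visit is 9 months after surgery

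*Protocol article*

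**What the plan says.** The timeline appears in the Abstract (Results), in the Results overview and in Table 2, and the three agree on the calendar dates.

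- Start: "Recruitment for this pilot single-arm study began in July 2025".
- Status: "As of October 2025, participant screening and baseline assessments were ongoing".
- Enrolment: "The target sample (N=22) is expected to be fully enrolled by January 2026".
- Surgery: the implant placement phase "is scheduled for completion by month 6 (April 2026").
- Visits: the clinical and radiographic evaluations "will be conducted at baseline, 3 months, and 9 months post surgery". The Abstract says the same: "Follow-up evaluations will be performed at baseline, 3 months, and 9 months post surgery".
- End: "Final data collection and statistical analysis are anticipated by month 12 (July 2026"). The July 2026 row of Table 2 reads "Completion of all follow-ups and commencement of statistical analysis".

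The Statistical Analysis section compares ISQ and bone density over baseline, 3 months and 9 months by repeated measures ANOVA. Bonferroni-adjusted comparisons of each pair of time points follow.

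**The concern.** The last visit is counted from surgery, so the earliest possible end of follow-up is the last surgery plus 9 months. The stated end date leaves a third of that interval. Two of the three planned pairwise comparisons (baseline with 9 months, and 3 with 9 months) and the overall ANOVA use the 9-month value. If the calendar were followed as written, participants operated on later would have no such value when the analysis starts. The Discussion also names follow-up to 9 months as a main strength of the design, so a reader will expect it to be complete.

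**Working it through.** **Inputs**, all from the Results overview and Table 2: recruitment from July 2025; enrolment complete by January 2026; surgery complete by April 2026 (labelled month 6); last visit 9 months after surgery; all follow-ups complete by July 2026 (labelled month 12).

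**1. Can the stated end date be reproduced?** End of follow-up = last surgery + 9 months. April 2026 + 9 months = January 2027 (1 to 30 January, depending on the day in April). The plan says July 2026. The gap from July 2026 to January 2027 is 6 months.

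**2. Follow-up available in July 2026.** July 2026 − April 2026 = 3 months. The last participants could have had the 3-month visit and nothing later.

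**3. Latest surgery that fits.** July 2026 − 9 months = October 2025 (31 October at the latest, taking 31 July 2026 as the end). Anyone enrolled after October 2025 must be operated on after it, and enrolment runs to January 2026.

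**4. Do the month labels rescue the dates?**

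| Reading | Consequence | Fits July 2026? |
|---|---|---|
| Labels only | Month 12 − month 6 = 6 months, short of 9 | No |
| July 2026 is month 12, so July 2025 is month 0 | April 2026 is month 9, not month 6 | No |
| Month 6 counted from July 2025 is right and the date April 2026 is wrong | Surgery ends January 2026; last visit October 2026 | No |
| April 2026 is month 6, so October 2025 is month 0 | Month 12 is October 2026; last visit January 2027 | No |

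The labels also disagree with each other. April to July is 3 calendar months, but month 6 to month 12 is 6.

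**5. How many participants?** The article gives no surgery dates, so this can only be illustrated under assumptions. The cut is 31 October 2025, for a 9-month visit by 31 July 2026.

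- Surgeries spread evenly from 1 July 2025 to 30 April 2026: 181 of 303 days lie after the cut, so 0.60 × 22 ≈ 13 would lack the visit.
- Surgeries keeping pace with enrolment, 1 July 2025 to 31 January 2026: 92/214 = 0.43, so 0.43 × 22 ≈ 9. This does not sit well with a surgical phase running to April.
- Surgeries starting in November 2025: all 22.

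The illustrations run from about 9 to 22 of 22. Surgeries concentrated early would give fewer.

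**The case against.** The July 2026 date is described as anticipated. The article sets no data cut-off, does not stop follow-up and does not exclude later visits. The visit schedule is tied to surgery and is consistent throughout, so the likely practical outcome is that the 9-month visits take place and the analysis is late. That stands. A reader might infer that participants will be dropped, or that 9-month results will be reported for a selected group of early cases. The article does not say so.

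A reader might also infer that most participants cannot reach 9 months in time. That rests on surgery dates which are not given. The October 2025 status mentions only screening and baseline assessments, but the Radiographic Measurements section takes the first ISQ immediately after implant placement, so baseline assessments could include operated participants. With surgery concentrated early, a majority could still reach 9 months by July 2026.

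A specific loss of power is not supported either. With the plan's f = 0.40 and correlation 0.5, a noncentral F calculation (noncentrality n × 3 × 0.16/0.5) gives 0.98 for 22 participants and 0.66 for 9. The 9 comes from an assumed pace of surgery (22 − 13 in the first illustration), and 0.98 does not match the 0.90 that the Sample Size Calculation states for 22.

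None of this removes the conflict. Table 2 says outright that all follow-ups are complete in July 2026, and no section describes an interim cut or a shorter follow-up. Nor is this a gap left by condensing a fuller protocol, because the dates are printed and disagree.

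**Conclusion.** The timeline is wrong as written. With surgery to April 2026 and a visit 9 months later, follow-up ends in January 2027, 6 months after the stated date. If the month 6 label is right and surgery ends in January 2026, it ends in October 2026, 3 months after the stated date. No reading of the labels gives July 2026. It follows from the printed dates alone that anyone operated on after October 2025 cannot have the 9-month value by July 2026. How many that is cannot be determined from the article; it is known only that enrolment was still open in October 2025 and was planned to January 2026. The article also does not show whether the error lies in the April date, the month label or the end date. The endpoints, visit schedule and analysis method are not in question here.

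**What to change.** In the Abstract, the Results overview and Table 2:

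1. Reconcile the surgery date, the end date and the month labels on one stated month 0. If that is July 2025 and April 2026 stands, April is month 9. If month 6 is the correct element, the date changes instead.
2. Set final data collection and the final analysis no earlier than the last actual surgery plus 9 months: January 2027 if surgery ends in April 2026, October 2026 if it ended in January 2026.
3. Label any report made in July 2026 as an interim descriptive report through 3 months, with no 9-month test or conclusion.

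The cost is corrected text and a final report about 3 to 6 months later. No extra participants or procedures are needed.

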### Expected Outcomes

It is hypothesized that osseodensification may enhance mechanical retention and primary implant stability by increasing peri-implant bone density and bone-to-implant contact. Within the scope of this pilot study, osseodensification is expected to demonstrate potential improvements in bone compaction and implant stability when compared to baseline values in D2-D3 bone sites.

Based on previous preclinical and limited clinical evidence, it is anticipated that osseodensification could contribute to improved early osseointegration and reduced micromotion. However, these outcomes remain to be verified, as this exploratory protocol is designed primarily to assess feasibility, short-term trends, and methodological reliability, rather than to establish definitive clinical efficacy.

The findings from this pilot study will therefore serve as preliminary data for refining hypotheses, estimating effect sizes, and informing the design of future RCTs comparing osseodensification with conventional osteotomy techniques.

## Discussion

### Principal Findings

The purpose of this study was to assess how osseodensification impacted implant stability and bone density following delayed implant implantation, specifically in locations with D2 and D3 bone quality. It is predicted that, in contrast to what has previously been seen with traditional osteotomy procedures, osseodensification will improve peri-implant bone compaction, raise insertion torque and RFA values, and help to produce more predictable osseointegration.

According to previous research, osseodensification may accelerate osseointegration, improve BIC, and maintain trabecular bone. For instance, osseodensification considerably raised primary stability and peri-implant bone density as compared to the baseline [24]. In preclinical animal models, it was shown that osseodensification leads to more compact peri-implant bone and enhanced secondary stability [13,17]. Comparing osseodensification to traditional drilling, retrospective clinical research [25] and systematic reviews [6,16] have also shown that osseodensification results in less marginal bone loss and fewer complications. Despite these promising findings, the majority of earlier research was restricted to retrospective analysis, ex vivo studies, or animal trials. In order to fill this gap, this study will provide prospective clinical data under controlled circumstances.

Achieving adequate primary stability in individuals with low bone density, especially those with D3 or D4 bone, is difficult and raises the risk of both early and late implant failures [26]. In order to prepare for an osteotomy, the traditional drilling method removes the bone, which could further reduce bone density and delay osseointegration and healing [27]. Huwais and Meyer [14] established the relatively new process of osseodensification in 2013, which compacts and autografts the bone along the osteotomy walls rather than removing it. Specially manufactured burs that rotate counterclockwise at regulated pressures and speeds are used to achieve this [5]. According to one comparative study [24], osseodensification enhances the initial mechanical stability of the implant, maintains bone mass, and increases peri-implant bone density.

Research contrasting osseodensification with traditional drilling has yielded encouraging results [28] and showed that implants inserted with osseodensification had more BIC and higher insertion torque than implants inserted using conventional drills. Similarly, even in low-density bone sites found that osseodensification improved implant stability in the posterior maxilla [15]. It was further shown in an animal investigation that osseodensification resulted in improved peri-implant bone compaction and more consistent bone growth along the osteotomy walls [13].

In addition, osseodensification has been shown to be helpful in enabling sinus floor elevation and ridge extension treatments without requiring extra grafting materials. Also, osseodensification has shown better results in sinus lift procedures because of the increased bone density and reported successful ridge expansion with osseodensification in narrow alveolar ridges [29].

Even if there is increasing evidence for osseodensification, some systematic reviews have stressed the necessity for larger, carefully planned randomized clinical studies to confirm these results [6]. In addition, to attain the stated benefits, operator expertise and accurate technique application are essential [30].

Also, osseodensification may reduce complications, according to clinical observations. According to a retrospective investigation [25], sites treated with osseodensification had lower rates of marginal bone loss and implant movement. Furthermore, osseodensification maintains the bone’s vascularity, which may lower the likelihood of peri-implantitis and early failures [16].

Osseodensification seems to reduce the amount of time needed for osseointegration in the healing process. Around implants inserted with osseodensification, a histologic investigation [31] showed enhanced new bone production and quicker bone remodeling. Furthermore, implants implanted with osseodensification showed less micromotion and improved secondary stability [17], which could help ensure long-term success.

This protocol’s prospective design, which includes systematic follow-up at baseline, 3, and 9 months, is one of its main strengths. It allows for the study of both early and intermediate changes in implant stability and bone density. Objective and repeatable outcome metrics are provided by the use of RFA for implant stability and CBCT for radiographic evaluation.

One of the retrospective cohort study [32] evaluated 163 patients (329 implants) treated in the posterior maxilla between 2005 and 2011, comparing implants placed in native bone, direct sinus lift with simultaneous implant placement, and direct sinus lift with delayed implant placement over a minimum follow-up of 5 years (mean 7.0, SD 1.9 years). Radiological parameters, including bone crest level, bone loss, and vertical bone gain, as well as implant success and survival, were analyzed. Bone loss and implant outcomes were similar across all groups, with no significant differences. Graft resorption occurred primarily during the first 12 months but stabilized thereafter, remaining consistent through 5 years of follow-up. Overall, implants placed in native bone or following sinus lift (simultaneous or delayed) showed comparable long-term success and survival, with early graft height reduction followed by stabilization [32]. In another retrospective study [33], less traumatic magnetoelectric versus conventional single-tooth extraction in premolar and molar sites were compared to evaluate alveolar ridge volume preservation. Forty-eight patients were allocated to the test group (20 sites, less traumatic extraction with tooth sectioning and magnetoelectric root subluxation) or control group (28 sites, conventional extraction). Alveolar socket contours were captured intraoperatively and at four months using a laser intraoral scanner, converted to Digital Imaging and Communications in Medicine format, and analyzed volumetrically and for surface area. Significant reductions in anatomical features were observed in all groups (*P*<.001), with mean final ridge volumes of 0.87 (SD 0.34) cm³ for less traumatic extractions and 0.66 (SD 0.19) cm³ for conventional extractions. In molar sites, volume loss was significantly lower with less traumatic extraction (Δ volume −0.30, SD 0.10 cm³, Δ volume % −22.3, SD 8.4%) versus conventional extraction (Δ volume −0.59, SD 0.10 cm³, Δ volume % −44.3, SD 5.8%; *P*<.001). Overall, less traumatic extraction better preserved alveolar crest volume, particularly in molar sites [33]. Another study evaluated the navigated antral bone expansion technique for implant placement in the atrophic posterior maxilla. Thirty-seven partially edentulous patients with 4-7 mm of residual bone were treated using navigated antral bone expansion to increase bone height. Pre- and postsurgical distances between the alveolar ridge and sinus floor were compared using paired-samples *t* tests, and angular deviations between planned and actual implant trajectories, as well as postsurgical complications, were assessed. Data from 35 patients showed a significant mean bone height increase of 3.96 (95% CI 3.62-4.30; *P*<.005) mm, with no postoperative complications observed. The mean angular deviation ranged from 12.7° to 34.9° (mean 25.17°, SD 5.10°). These findings suggest that the navigated antral bone expansion technique provides a significant and minimally invasive bone augmentation option for managing the atrophic posterior maxilla [34].

Nonetheless, it is necessary to recognize some limitations. Since improvements will only be evaluated in relation to baseline values, the single-arm design without a comparator group (conventional osteotomy) limits the capacity to draw concrete conclusions about the superiority of osseodensification. The 9-month follow-up period might not accurately represent long-term implant survival and performance, even though it is long enough to record short- to midterm outcomes of implant stability and bone density. Given the technical sensitivity of osseodensification, operator-related procedure variability may also affect results, even with calibration efforts. In addition, while the inclusion criteria, which concentrate on individuals with intact alveolar walls, adequate oral hygiene, and D2-D3 bone quality, lessen confounding, they may also introduce selection bias and restrict external validity to more diverse real-world populations.

In both high- and low-density bone sites, the findings of this exploratory study will be used as pilot data to guide the design of RCTs that compare osseodensification with traditional drilling. The impact of baseline patient characteristics, including bone quality, systemic diseases, oral hygiene level, or site location on the efficacy of osseodensification should also be investigated in larger research. Furthermore, to demonstrate the external validity and practicality of this method, practical clinical trials with bigger and more varied patient groups would be required.

Presentations at national and international dental research conferences and the submission of full-length publications to peer-reviewed journals will be used to share the trial’s findings. To help with knowledge translation and incorporation into clinical practice, the results will also be shared with the institution’s participating patients and doctors.

It is anticipated that the trial will demonstrate, within the constraints of this single-arm exploratory protocol, how osseodensification may improve bone density and implant durability in delayed implant implantation at locations with D2 and D3 bone quality. The expected results will assist in establishing feasibility, produce effect size estimates, and guide the design of future RCTs that can more definitively evaluate the role of osseodensification in implant dentistry, even though definitive conclusions cannot yet be formed.

### Conclusions

The osseodensification approach exhibits encouraging potential to improve bone density, implant stability, and early osseointegration in delayed implant placement, especially in D2-D3 bone sites, within the constraints of this current single-arm pilot trial. Osseodensification may be able to get around the drawbacks of traditional osteotomy by conserving and compacting native bone instead of removing it, creating a more advantageous biomechanical environment for implant integration and long-term success.

The standardized clinical and radiographic technique used in this trial will produce important preliminary evidence regarding the feasibility and biological benefits of osseodensification, albeit conclusive outcome data are still lacking. The findings will help determine evidence-based clinical guidelines for maximizing implant success in impaired bone conditions, assist in the establishment of more substantial RCTs, and promote the improvement of future protocols.

